Currently marketed formulations of tacrolimus, such as Prograf® and Advagraf™, exhibit limitations primarily in terms of pharmacokinetic properties and tolerability. Tacrolimus has a narrow therapeutic index; blood trough level concentrations between 3 and 15 ng/ml are recommended during the first year after transplantation, provided that tacrolimus is given in combination with mycophenolate, steroids and induction with an anti-CD25 antibody [4]. Tacrolimus levels below this recommended range bear the risk of graft rejection, whereas levels above this range result in increased toxicity (e.g. nephrotoxicity, diabetes, tremor, hypertension) and increased susceptibility to opportunistic infections and malignancies [5].

Both Prograf® and Advagraf™ exhibit significant inter- and intra-individual variability in absorption owing to interactions with food and concomitant medications; also functional polymorphisms in the cytochrome P-450 system cause inconsistencies. In addition, both Prograf® and Advagraf™ exhibit a rather low bioavailability due to poor water solubility and pre-systemic gastrointestinal metabolism [6, 7]. As a result of this variability, standard dosing based on body weight is not an accurate predictor of drug exposure, and regular assessment of tacrolimus blood trough level concentrations is essential to measure effective drug exposure [8]. Currently, life-long monitoring of tacrolimus whole blood trough levels is required for all transplant patients [9].

Transplant recipients also typically require an array of concomitant medications for comorbidities, which means that interaction and tolerability profiles may cause issues. In addition, the intake schedule of many different medications may not easily be integrated into the patients’ daily life, which increases the risk of low patient compliance. As non-compliance with immunosuppressant dosing can result in graft rejection and failure, the once daily formulation of tacrolimus, Advagraf™, was designed to reduce the daily pill burden compared to Prograf® (taken twice daily). However, this potential benefit of Advagraf™ is counterbalanced by delayed achievement of therapeutic trough levels after transplantation and the need for an up to 50% higher dosage to maintain trough levels similar to Prograf® [10], therefore jeopardising tolerability.

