**Fig. 3 Fig3:**
[figure not shown]
Tac measurements. Minimum schedule of tacrolimus trough level measurements

C/D ratio tends to fluctuate during the first weeks and months after transplantation. Twelve weeks post-randomisation (visit 7) has therefore been chosen for timing of the primary endpoint because the overall metabolic situation in patients is expected to be stable by this time. Also, at 12 weeks, the influence of concomitant immunosuppressive agents that may affect C/D ratio should be less pronounced. Corticosteroids are often concomitantly administered with tacrolimus and are allowed as non-investigational medication products (NIMP) in the EnGraft study. Since they share some common metabolic and transporter pathways with tacrolimus, higher steroid doses and rapid steroid tapering during the early post-transplant period may interfere with tacrolimus metabolism and destabilise the C/D ratio [18, 27]. At the 12-week time point, the use of steroids should have been tapered and the C/D ratio sufficiently stable to provide an accurate estimate of tacrolimus bioavailability.

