## Interventions

### Randomisation

A dynamic allocation technique will be used for randomisation of patients fulfilling the trial eligibility criteria in a 1:1 ratio to one of two treatment arms: Envarsus® tablets (test IMP) or Advagraf™ capsules (comparator IMP). Pre-treatment with immediate-release tacrolimus (Yes/No), as well as trial site, will be used as stratification factors in the treatment allocation to minimise sources of treatment bias. The first stratification factor (study centre) will minimise systematic treatment bias at the study centre level and reduce the influence of inter-centre variability. The second stratification factor (pre-treatment with immediate-release tacrolimus) will minimise treatment bias at the level of the individual patient, since patients treated with Prograf® during the run-in phase can be expected to develop stable trough levels after randomisation more rapidly than patients who do not receive Prograf® prior to commencing IMP. Balancing the treatment arms with respect to this factor allows fair and unbiased evaluation of the secondary pharmacokinetic endpoints that evaluate the ease with which the first target trough level is achieved.

The allocation algorithm is programmed into a randomisation module in the trial database. Study investigators at the participating trial sites have access to the randomisation module via the online trial database and randomise using this central tool. It is vital that randomisation is performed as soon as possible after eligibility has been confirmed and no later than 14 days after transplantation surgery; enrolment after this time period is not allowed.

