### Non-investigational medical products

In this trial, it is medically necessary in most cases for clinical trial subjects to receive a multi-drug immunosuppressive regimen to prevent allograft rejection. Therefore, in addition to IMP, patients will be treated with a therapy of several other immunosuppressive agents, regardless of randomisation group. All systemic immunosuppressive therapy given will be collected in the eCRF.

The following substances are prohibited during study participation:CyclosporineAny tacrolimus preparation other than the assigned IMP (excluding immediate-release formulations taken prior to randomisation or during an acute rejection episode or in place of the IMP during a temporary interruption of IMP)St. John’s wort (*Hypericum perforatum*)Grapefruit and grapefruit juice

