### Visit 1—Baseline

At the baseline visit (visit 1), patients are randomised and baseline characteristics are measured. The date of the baseline visit is designated as trial “day 0” and must occur no later than 14 days after transplantation surgery.

In case the run-in phase is skipped, all screening procedures must be performed at the baseline visit prior to randomisation. Randomisation may take place only after all eligibility criteria have been checked and fulfilled.

The following baseline procedures/data will be performed/collected (the applicable panel of assessments is displayed in Fig. 4):Randomisation, dispensing of assigned IMP, explaining practicalities of drug administration to the patientPatient characteristics, including demographicsPast medical historyDonor and transplantation dataPhysical examination, including body weight12-lead ECGVital signs: blood pressure, pulse rate, body temperatureBlood sampling for clinical tests:◦ Haematology, serum biochemistry, including calculation of eGFR◦ Blood coagulation screen◦ Virology status: CMV, EBV, HCV, HBV◦ Tacrolimus trough level (if immediate-release tacrolimus given prior to randomisation)Urine sampling for clinical urine analysisReview and documentation of concomitant medication that interacts with IMP or is prohibited per protocol

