### Sample size calculation

Sample size estimation is based on testing superiority of Envarsus® versus Advagraf™ with respect to the primary efficacy variable. C/D ratio data obtained from previously published clinical trials in kidney transplantation and observational studies in LTx inform an assumed difference between the two treatments Envarsus® or Advagraf™ after 12 weeks of approximately 0.4 with a standard deviation of 1.0.

A sample size of 100 patients per treatment group will have the power of 80% to show a difference of 0.4 in C/D ratio between the two treatment groups with a two-sided significance level of 5%. The primary test will be performed based on the Full Analysis Set (FAS) but will be repeated for the Per-protocol analysis set (PPAS). To have a sufficient power also for the PPAS comparison, it is planned to randomise 134 patients in each treatment group assuming that about 25% of randomised patients cannot be included in the PPAS because of major protocol deviations. A sample size of 134 patients per treatment group will have a 90% power to show a difference of 0.4 in C/D ratio in the FAS. The minimal detectable difference in the FAS will be 0.24.

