### Primary endpoint

The aim of the EnGraft Study is to show that Envarsus® is superior to Advagraf™ with respect to the primary variable, which is defined as the C/D ratio at week 12 after randomisation.

The analysis of the primary endpoint will be performed by means of analysis of covariance considering randomised treatment and pre-treatment with immediate-release tacrolimus (stratification factor) as fixed effects in the model. Least square means, standard errors, treatment difference and corresponding 95% confidence intervals will be reported.

The primary population for analysis of the primary endpoint, secondary efficacy endpoints and secondary pharmacokinetic endpoints will be the FAS. Supportive analyses will be carried out for the PPAS.

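### The primary analysis of covariance names no continuous baseline covariate; prespecifying baseline body weight would be a nearly free, low-priority gain in precision

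*Protocol article*

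**What the plan says.** Under Statistical analysis, Primary endpoint, the protocol article gives the model as "analysis of covariance considering randomised treatment and pre-treatment with immediate-release tacrolimus (stratification factor) as fixed effects in the model". No other term is listed. The Randomisation section says "Pre-treatment with immediate-release tacrolimus (Yes/No), as well as trial site, will be used as stratification factors", so the pre-treatment term is a baseline stratification factor.

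The endpoint is the trough level at visit 7 divided by the daily dose taken the day before (Objectives, Primary endpoint, and Fig. 2). The dose is in mg and is not scaled to body weight, whereas the starting doses of both products are given per kg (Investigational group; Control group).

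The Visit 1—Baseline list includes body weight for all patients. It also includes "Tacrolimus trough level (if immediate-release tacrolimus given prior to randomisation"), so a baseline trough exists only in pre-treated patients. That list does not itemise the tacrolimus dose given before randomisation. The nearest statement, under Non-investigational medical products, is general: "All systemic immunosuppressive therapy given will be collected in the eCRF".

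The Sample size calculation assumes a difference "after 12 weeks of approximately 0.4 with a standard deviation of 1.0" and takes no credit for covariates.

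**The concern.** An analysis of covariance normally earns its name by adjusting for a continuous baseline measurement that predicts the outcome. With one treatment factor and one yes/no stratum, the stated model is in effect a two-way analysis of variance. The standard deviation, 1.0 against a difference of 0.4, governs the power, so any part of it explained by a baseline value narrows the confidence interval without more patients.

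Body weight is the natural candidate. It is recorded for everyone, it is known at day 0 and so cannot be affected by the randomised treatment, and the denominator of the endpoint is an unscaled mg dose. A pre-randomisation C/D ratio is a second candidate in pre-treated patients, because the article treats the C/D ratio as a marker of how a patient metabolises tacrolimus.

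Only efficiency is at stake: the width of the interval and some power, chiefly in the smaller per-protocol set. The validity of the comparison is not in question.

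**Working it through.** **Inputs from the Sample size calculation.** Difference 0.4; SD 1.0; two-sided 5%; 100 per arm for 80% power; 25% loss to the per-protocol set (PPAS); 134 per arm; 90% power in the Full Analysis Set (FAS); minimal detectable difference 0.24.

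**Input not in the documents.** The share of variance explained, R², is assumed to lie between 1% and 10%.

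**Step 1: reproduce the plan's figures without covariates.** The standard error of the difference is SD × √(2/n).
- n = 100: 1.0 × √(2/100) = 0.1414; noncentrality 0.4/0.1414 = 2.83; noncentral-t power 80.4%.
- Loss: 100/0.75 = 133.3, rounded up to 134.
- n = 134: 1.0 × √(2/134) = 0.1222; noncentrality 0.4/0.1222 = 3.27; power 90.4%.
- Minimal detectable difference: 1.96 × 0.1222 = 0.24.

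Every stated figure reproduces, so the plan does not depend on covariate adjustment.

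**Step 2: effect of adjustment.** The residual SD becomes √(1 − R²); the number per arm with equal information is 134/(1 − R²).

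| Assumed R² | Residual SD | Power, 134 per arm | Power, 100 per arm | 95% CI half-width, 134 per arm | Equivalent n per arm |
|---|---|---|---|---|---|
| 0 | 1.000 | 90.4% | 80.4% | 0.239 | 134 |
| 1% | 0.995 | 90.6% | 80.8% | 0.238 | 135 |
| 5% | 0.975 | 91.7% | 82.3% | 0.233 | 141 |
| 10% | 0.949 | 93.0% | 84.3% | 0.227 | 149 |

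The half-width is 1.96 × residual SD × 0.1222. A single covariate with correlation r has R² = r², so the 1% and 10% rows correspond to r = 0.10 and r of about 0.32.

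**Step 3: a covariate that exists only in pre-treated patients.** If a share f is pre-treated and the correlation among them is r, the overall R² is about f × r². Neither value is in the documents. With f = 0.5 and r = 0.3 (assumed), R² = 0.5 × 0.09 = 4.5% and FAS power is 91.6%.

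**Step 4: cost if a covariate predicts nothing.** The stated model leaves 268 − 3 = 265 residual degrees of freedom. Each added term uses one and, through chance imbalance, inflates the variance of the treatment difference by roughly 1/265, or 0.4%. One term therefore breaks even at an R² of about 0.4%; three terms together break even at about 3 × 0.4% = 1.1%.

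**The case against.** The strongest reply is that nothing here is wrong. The model is prespecified and unbiased, and the planned power is met without covariates. The SAP is not shown and may add terms. All of this stands, and it is why the point ranks low. It does not change the fact that the article lists its model terms and that body weight is not among them.

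The link with weight can also be doubted. The dose in the endpoint is the one reached after 12 weeks of titration to a trough target, not the per-kg starting dose, and the Background says "standard dosing based on body weight is not an accurate predictor of drug exposure". This is fair: the per-kg starting rule does not establish a correlation at week 12. But a poor guide to an individual's exposure can still be associated with the mg dose that patients end up needing. The size of the gain is unknown, and adjustment remains harmless.

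The case for a pre-randomisation C/D ratio is weaker. The text after Fig. 3 says "C/D ratio tends to fluctuate during the first weeks and months after transplantation". The value would come from another formulation within 14 days of surgery, would be absent in patients not pre-treated, and needs a dose that visit 1 does not itemise. Nesting it within the pre-treatment factor is valid, but that does not make it predictive.

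A reader might infer more than the documents support:
- **That the model has no baseline covariate at all.** Pre-treatment is a baseline factor and is in it.
- **That much of the between-patient spread is a fixed patient trait.** The Background names food and concomitant medication, then adds that "functional polymorphisms in the cytochrome P-450 system cause inconsistencies", and gives no shares.
- **That baseline level and dose are both available.** The level is listed for pre-treated patients only; recording of the dose is an inference from a general statement.
- **That a large gain is being lost.** An R² of 20%, for example, would equal 134/0.8 = 167.5, or about 34 more patients per arm, but no R² can be taken from the documents.

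**Conclusion.** The point holds as an efficiency suggestion. The stated primary model contains no continuous baseline covariate, although body weight is recorded for all patients and is plausibly related to a per-mg ratio. There is no bias, no contradiction and no shortfall against the stated power.

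The likely size is modest: with R² between 1% and 10%, about 0.3 to 2.7 percentage points of FAS power and 0.4 to 3.9 points at 100 per arm. These figures rest on the plan's own difference and SD, complete week-12 data and an assumed R². They show a range and are not evidence of harm. Body weight carries the recommendation; the pre-randomisation C/D ratio is optional. Priority is low.

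**What to change.** Add baseline body weight (visit 1 value) as a continuous covariate to the primary model, beside randomised treatment and the pre-treatment factor. Fix this in the SAP before any week-12 central trough result is seen. Report the model without it as a sensitivity analysis.

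Optionally, first confirm that the pre-randomisation oral tacrolimus dose is usable in the eCRF. If it is, add pre-randomisation C/D nested within the pre-treatment factor: value 0 if not pre-treated, with a separate indicator for pre-treated patients who have no oral trough. Accept in advance that it may predict little.

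The cost is SAP wording and one degree of freedom for weight, or three with the optional terms, out of 265. Body weight needs no new visit, sample or data item; the optional term needs the check on the dose record.

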### Secondary endpoints

All secondary variables will be analysed by treatment group using descriptive statistical methods. Secondary efficacy variables for the controlled treatment phase may be analysed between the two groups using two-sided testing with nominal significance level *α* = 0.05 and are to be interpreted in a strictly exploratory sense. If appropriate, two-sided 95% confidence intervals will be provided.

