A new once-daily formulation of tacrolimus, Envarsus®, was approved in 2014 by the European Medicines Agency (EMA) for the prophylaxis of rejection in kidney or liver allograft recipients and treatment of rejection resistant to other immunosuppressants [11]. Envarsus® is a prolonged-release formulation of tacrolimus developed using MeltDose™ drug-delivery technology, which increases the bioavailability of poorly water-soluble compounds via solid formulation at molecular state. Improvement in the bioavailability of Envarsus®, which allows once-daily administration, results in lower inter- and intra-patient variability of drug absorption with reduced peak-to-trough fluctuation and earlier achievement of a stable tacrolimus profile, as demonstrated in healthy volunteers [12]. In phase III studies using stable, de novo kidney transplant patients, Envarsus® has proven to be non-inferior to twice-daily tacrolimus in terms of treatment failure, a composite trial endpoint of death, graft failure, acute rejection or lost-to-follow-up [13, 14]. Additional potential benefits of Envarsus® are reduced pill burden and diminished peak-related toxicities such as tremor [15].

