**Fig. 2 Fig2:**

Calculation of C/D ratio. In this formula, “C” represents the trough level measured in a blood sample collected immediately prior to drug dosing on the day of a trial visit (*t*_0_) and “D” denotes the daily dose taken by the patient on the day prior to the visit (*t*_-1_)

A centralised measurement of the 12-week tacrolimus blood trough level at the University Hospital Regensburg will be used to calculate C/D ratio for the primary endpoint.

During the controlled treatment phase (first 12 weeks post-randomisation), tacrolimus should be dosed by the investigator to reach and maintain whole blood trough concentrations within the general reference range of 3–12 ng/ml. For every randomised patient, a narrower target range (with an interval of 3 ng/ml) within the wider reference range of 3–12 ng/ml is to be defined at all times and continually reviewed/revised based on clinical circumstances. The first target range is to be set prospectively by the investigator and documented in the eCRF at baseline to enable analysis of the pharmacokinetic endpoints. Since the frequency of trough level measurement directly influences pharmacokinetic endpoints, each trial centre aims to follow the minimum schedule of trough level measurement outlined in Fig. 3.

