### Investigational group

Envarsus® will be supplied by the sponsor for the duration of the 12-week controlled treatment phase. Envarsus® will not be supplied for the follow-up phase (Table 1).

**Table 1 Tab1:** IMP-characteristics of Envarsus®

IMP name	Envarsus®
Active ingredient	Tacrolimus monohydrate
Pharmaceutical form	Prolonged-release tablet
Presentation	Oval, white to off-white uncoated tablet
Administration	Once daily, oral formulation provided in 0.75 mg, 1.0 mg and 4.0 mg dosage strengths

Envarsus® therapy should commence at a starting dose of 0.11–0.13 mg/kg/day.

In case the patient initially received an oral formulation of Prograf® during the run-in phase (e.g. administered via nasogastric tubing), conversion should be performed on a 1:0.7 (mg to mg) total daily dose basis. In case the patient initially received intravenous Prograf® therapy (continuous 24-h infusion) during the run-in phase at a dose approximately 1/5th of the recommended oral dose, the conversion to Envarsus® should be modified accordingly.

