### Control group

Advagraf™ will not be provided by the sponsor, but supplied/prescribed as per site routine (Table 2).

**Table 2 Tab2:** IMP-characteristics of Advagraf™

IMP name	Advagraf™
Active ingredient	Tacrolimus monohydrate
Pharmaceutical form	Prolonged-release hard capsule
Presentation	Gelatin capsule with light yellow/white/orange/greyish-red capsule cap on an orange capsule body containing white powder in respectively 0.5 mg/1 mg/3 mg/5 mg dosage strengths
Administration	Once daily, oral formulation provided in 0.5 mg, 1.0 mg, 3.0 mg and 5.0 mg dosage strengths

Advagraf™ therapy should commence at a starting dose of 0.1–0.2 mg/kg/day.

In case the patient initially received an oral formulation of Prograf® during the run-in phase (e.g. administered via nasogastric tubing), conversion should be performed on a 1:1 (mg to mg) total daily dose basis. In case the patient initially received intravenous Prograf® therapy (continuous 24-h infusion) during the run-in phase at a dose approximately 1/5th of the recommended oral dose, the conversion to Advagraf™ should be modified accordingly.

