## Discussion

Tacrolimus is an effective immunosuppressive drug that is used immediately and long-term in the majority of LTx recipients. Currently available tacrolimus formulations are characterised by high inter- and intra-variability, high peak levels and low bioavailability, often creating problems in clinical efficacy. Envarsus® is manufactured using MeltDose technology and represents an innovation in the field of immunosuppressive drugs. This galenic formulation increases the amount of active ingredient that reaches the blood, ensuring higher therapeutic efficacy. In a phase 2 study conducted on stable LTx patients [28], pharmacokinetic data demonstrated consistent exposure at a lower conversion dose. In 2019, Baccarani et al. [22] retrospectively compared Envarsus® versus Advagraf™ in de novo LTx recipients, focusing on administered daily dose and therapeutic trough levels during the first 30 days after transplant. Using Envarsus® resulted in faster achievement of therapeutic trough levels. Moreover, after stabilisation of tacrolimus blood levels, patients given Envarsus® required a 25% lower median dose of administered drug to maintain the same therapeutic trough level compared with Advagraf™. Furthermore, Grinyó et al. [29] showed in 2014 approximately 30% lower dosing benefit using Envarsus® compared to twice-daily tacrolimus capsules (e.g. Prograf®). Tacrolimus levels below the recommended range bear the risk of graft rejection, whereas levels above this range result in increased toxicity (e.g. nephrotoxicity, diabetes, tremors, hypertension) and increased susceptibility to opportunistic infections and malignancies [5]. Using the MeltDose technology, Envarsus® shows a lower intra-day fluctuation in tacrolimus blood concentration compared to Advagraf™ [19]. Therefore, potential benefits of Envarsus® are reduced pill burden and diminished peak-related toxicities such as tremors [15]. Thus, these factors will be measured and quantified by the secondary endpoints we have chosen.

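### Inter-patient variability of total daily dose is measured by the range in mg, which shrinks with the lower Envarsus dose and would pass off a dose saving as lower variability

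*Protocol article*

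**What the plan says.** Under Selected secondary endpoints, the protocol article lists inter-patient variability of tacrolimus total daily dose up to week 12, with the range named in brackets as the measure. The same bracketed measure is attached to trough levels at weeks 1, 2, 4 and 12. No scale-free measure is named for either.

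The Secondary endpoints part of the analysis section says "All secondary variables will be analysed by treatment group using descriptive statistical methods". Any between-group tests use a nominal two-sided 5% level and "are to be interpreted in a strictly exploratory sense".

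Three other places bear on how the dose range will behave:

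- **Dose level.** The Discussion reports, from a retrospective comparison in de novo liver recipients, that "patients given Envarsus® required a 25% lower median dose of administered drug to maintain the same therapeutic trough level compared with Advagraf™". For patients who had oral Prograf in the run-in phase, the Envarsus section says "conversion should be performed on a 1:0.7 (mg to mg) total daily dose basis" and the Advagraf section says "conversion should be performed on a 1:1 (mg to mg) total daily dose basis".
- **Trough target.** Both arms are dosed to reach "whole blood trough concentrations within the general reference range of 3–12 ng/ml".
- **Expected advantage.** The Background says that the improved bioavailability of Envarsus "results in lower inter- and intra-patient variability of drug absorption with reduced peak-to-trough fluctuation", citing healthy volunteers.

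**The concern.** A range carries the units of the thing measured. If one product needs fewer milligrams for the same exposure, every dose in that arm shrinks by about the same factor, and so does the gap between the largest and smallest dose. Patients may differ from one another exactly as much, in relative terms, as in the other arm.

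The article itself expects the Envarsus dose to be lower. The dose endpoint is therefore likely to show a narrower Envarsus range whether or not patients on Envarsus vary less. The artefact runs in the direction of an advantage that the Background already attributes to Envarsus. A reader who sees a range about a quarter narrower, under the label of inter-patient variability, may take it as confirmation. Much of it would be the dose saving that the primary C/D ratio already captures.

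**Working it through.** **Inputs from the protocol article**

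- Dose ratio, Envarsus to Advagraf: 0.75 from the 25% lower median dose (Discussion), or 0.7/1 = 0.70 from the two conversion rules (Investigational group, Control group).
- Patients per arm: 134 (Sample size calculation).
- Trough reference range: 3–12 ng/ml in both arms (Primary endpoint, text after Fig. 2).

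**Inputs assumed, because the article does not give them**

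- Doses are log-normal.
- The between-patient CV is the same in both arms, taken over 30–70%.
- The Advagraf mean is 8 mg/day. This sets only the mg scale and cancels from every ratio.

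**Step 1: the plan's own figures.** The article states no figure for the range endpoints. Its sample size rests on a difference "after 12 weeks of approximately 0.4 with a standard deviation of 1.0" and reproduces:

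- 99 per arm for 80% power (stated: 100).
- 100/0.75 = 133.3, so 134 after 25% loss.
- Power of 80.7% at 100 per arm and 90.6% at 134 per arm.
- Minimal detectable difference 1.96 × √(2/134) = 0.239 (stated: 0.24).

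Nothing below changes these.

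**Step 2: scaling.** For any factor k, range(kX) = k × range(X). The CV, the SD of log X and max/min do not change with k. With k = 0.75 or 0.70 and equal relative variability, the expected range ratio is 0.75 or 0.70, that is, 25% or 30% narrower.

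**Step 3: how often the range favours Envarsus when relative variability is equal** (20,000 simulated trials per row, 134 per arm)

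| CV in both arms | Dose ratio | Mean range, Advagraf vs Envarsus (mg) | Ratio | Envarsus range smaller | Envarsus CV smaller |
|---|---|---|---|---|---|
| 30% | 0.75 | 13.04 vs 9.79 | 0.751 | 90.4% | 49.7% |
| 30% | 0.70 | 13.02 vs 9.13 | 0.701 | 94.6% | 49.5% |
| 50% | 0.75 | 22.95 vs 17.19 | 0.749 | 83.1% | 50.0% |
| 50% | 0.70 | 22.86 vs 16.06 | 0.703 | 88.2% | 49.8% |
| 70% | 0.75 | 34.03 vs 25.59 | 0.752 | 78.0% | 49.8% |
| 70% | 0.70 | 34.16 vs 23.80 | 0.697 | 83.3% | 50.4% |

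Over the middle band, CV 40–60% with either dose ratio, the Envarsus range is the smaller one in roughly 80–91% of trials. The SD of log dose gives about 50%.

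**Step 4: Envarsus truly more variable.** With CV 55% on Envarsus against 50% on Advagraf, and a median dose ratio of 0.75, the range still favours Envarsus in about 70% of trials. The SD of log dose does so in about 16–17%.

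**Step 5: trough.** Both arms aim at the same reference range, so no factor k is expected. With a common mean (assumed 7.5 ng/ml) and a CV of 30%, 40% or 50%, the mean ranges agree to within 0.3% and Envarsus has the smaller one in 50% of trials. There is no directional bias.

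**Step 6: precision, either endpoint.** At equal level and CV 50%, the simulated 95% sampling interval of the range ratio is about 0.55–1.83. For the ratio of log SDs it is about 0.84–1.19. The second agrees with the approximation exp(±1.96 × √(2/(2 × 133))) = exp(±0.170), which gives 0.84–1.19.

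**The case against.** The strongest reply is that little hangs on this. The endpoint is secondary, testing is optional and exploratory, and no success criterion uses the range. The list is headed as a selection, and the full protocol and SAP are not shown. Descriptive methods leave room for an SD or CV, and choosing a dispersion statistic is often SAP work. Spread in mg is also a legitimate description of practicability. The simulated percentages rest on assumed distributions and count only which arm's range is smaller.

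Much of this stands, and it limits the weight of the point. It does not remove it. The article does not leave the measure open: it names the range beside the endpoint. The scaling in Step 2 needs no distributional assumption, only a dose lower by a common factor. Exploratory status limits what a p-value may claim, but it does not take a one-directional artefact out of a descriptive table.

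Three stronger readings might be inferred, and the documents do not support them:

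- **That the trough range is biased in the same way.** Both arms are dosed to one reference range, so needing fewer milligrams does not lower the trough.
- **That the trial cannot address variability, or that a trough range cannot show a real difference.** The stated aims are bioavailability, practicability and the C/D ratio, and C/D is calculated at several time points. With trough CVs of 32% against 40% and equal medians, the range points the right way in about 87% of simulated trials, although imprecisely (ratio 0.47–1.24).
- **That the sentence on descriptive analysis is wrong.** It is not. The measure named in the endpoint list is what misleads.

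**Conclusion.** The point holds for total daily dose only. The range in mg is the named measure, and the article's own figures predict a lower Envarsus dose. At equal relative variability the expected Envarsus range is 25–30% narrower.

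That size rests on the article's 25% lower median dose and its 1:0.7 conversion carrying over to this trial as a roughly common factor. The conversion rule applies only to patients pre-treated with oral Prograf. The 80–91% figure also assumes log-normal doses, CV 40–60% and 134 patients with data in each arm. At CV 30–70% the table gives 78–95%.

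For trough there is no dose-scaling bias, and a better statistic there gains precision only. An unseen SAP may already add a scale-free measure. The primary comparison, its power and the sample size are untouched.

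**What to change.** In the endpoint list, define inter-patient variability of total daily dose by the geometric CV in each arm, computed as √(exp(s²) − 1) with s the SD of log dose. Take it at fixed visits, for example the weeks 1, 2, 4 and 12 already used for trough. Report the between-arm ratio with its 95% CI. Keep minimum and maximum as ordinary summary statistics and draw no variability claim from them.

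For trough, report the SD or geometric CV beside the range, for precision. Dividing each trough by the midpoint of the patient's current target window is not recommended. The article explicitly requires only the first window in the eCRF and lets the window be revised, so the data for later visits are not assured.

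A log-scale measure removes the scaling effect but not every influence on dose spread. Body weight, individual trough targets and the different starting-dose windows in the two arms remain. Early visits should be read with that in mind, and week 12 is the more informative one.

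The cost is a change of wording and a few lines of code, with no new data, visits or patients. If the SAP already specifies a scale-free measure, aligning the endpoint wording with it is enough.
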